### Participants

#### Inclusion criteria

Participants who meet all of the following criteria will be eligible to participate:Aged 55–90 years, with complaint of impaired memoryObjective cognitive impairment as measured by the Seoul Neuropsychological Screening Battery (SNSB), with a score of 3 on the Global Deterioration Scale (GDS), 0.5 on the Clinical Dementia Rating (CDR), and a normal score on the Korean MMSE (K-MMSE)Diagnosed with aMCI by a neurologistParticipants who have not taken medication affecting cognitive function, including gliatilin, gliatamine, ginexin, tanamin, or other psychoactive drugs, in the previous 2 weeksParticipants who have not changed medication for underlying diseases in the previous 2 weeks, and no expected change in medication during the study periodNo difficulty in communicating

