### Outcome

Primary outcomes will include changes in cognitive function, and changes in imaging biomarkers, before and after taking KGT or placebo granules. For assessing cognitive function, the SNSB will be conducted and changes in SNSB results will be analyzed. For measuring the imaging biomarkers, brain MRI scans will be taken to assess the levels of brain metabolites, neurotransmitters, and cerebral blood flow (CBF).

Secondary outcomes will include the safety of KGT granules, and changes in blood-based biomarkers including proteins (amyloid β (Aβ) and tau) and cholesterols, and a comparison of MRI changes between the two groups using age and genotype as covariates. For safety assessments, blood chemistry tests for AST/ALT, glucose, blood urea nitrogen (BUN), Cr, Na, K, Cl, lactate dehydrogenase (LDH), creatine phosphokinase (CPK), and an electrocardiogram (ECG) will be conducted. Blood biomarkers including Aβ protein, tau protein, high-mobility group box (HMGB), small EDRK-rich factor (SERF) 1A, and cholesterol derivatives will also be measured. *APOE* genotype testing will be performed. Detailed explanations are shown below.

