#### MRI

Participants will undergo brain MRI at baseline and after 24 weeks of medication, to measure changes in brain metabolite and neurotransmitter levels, cerebral blood flow, tissue volume, and to evaluate brain abnormalities.

Proton magnetic resonance spectroscopy (^1^H-MRS) will be used to measure brain metabolite and neurotransmitter levels. Single-voxel Point-RESolved Spectroscopy (PRESS) MRS will be performed at the precuneus and posterior cingulate area of the brain, with a voxel size of 30 mm × 30 mm × 30 mm, to detect *N*-acetylaspartate (NAA) and glutamate-glutamine complex (Glx, with both Glu and Gln). *N*-acetylaspartate and Glx will be quantified using LCModel software. MEshcher-GArwood (MEGA) PRESS MRS will be performed to detect gamma-aminobutyric acid (GABA) in the same area as the PRESS MRS. The amount of GABA will be quantified using GANNET software. Pseudo-continuous arterial spin-labeling (pCASL) MRI will be performed to measure cerebral blood flow (CBF) in the brain. Voxel-based CBF will be mapped using local software. A three-dimensional T1-weighted image will be acquired using the magnetization-prepared rapid gradient-echo (MPRAGE) sequence, to quantify the gray and white matter tissue volume in the brain. T2-weighted turbo-spin echo (TSE), and fluid attenuation inversion recovery (FLAIR) sequences, will be used to evaluate brain abnormalities in participants. Changes in CBF and mean levels of NAA/Cr, Glx/Cr, and GABA/Cr, will be compared between KGT and placebo groups, as a primary outcome.

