#### Blood testing

Amyloid β protein, tau protein, HMGB, SERF 1A, and cholesterol derivatives will be measured in the blood at baseline and after 24 weeks of medication to observe changes in serum proteins and cholesterol associated with AD pathology. Changes in mean values of blood biomarker levels will be compared between the KGT and placebo groups.

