#### Data analyses

The investigators, along with an independent professional statistician, will perform the data analyses. All statistical analyses will be performed using SPSS for Windows. The effectiveness test will be performed using the intention-to-treat (ITT) principle and the per-protocol (PP) principle. Missing data will be adjusted with the last-observation-carried-forward (LOCF) imputation method. The safety test will be analyzed using the ITT principle, without adjustment. We will not perform interim analysis.

The student’s *t* test will be used for parametric variable comparisons between the two groups, and the paired *t* test will be used for intra-group comparisons. The Mann-Whitney *U* test will be used for non-parametric variable comparisons between the two groups, and the Wilcoxon signed-rank test will be used for intra-group comparisons.

The paired *t* test will be used to compare changes in MRI measurements, blood proteins, and cholesterol levels, before and after treatment. Correlation analysis will be used to estimate the relationship between the changes in MRI measures and changes in blood test results. Linear regression analysis will be used to compare changes in MRI measures, between the study group and the placebo group, using age and *APOE* genotype as covariates. Statistical significance will be set at *P* < 0.05, and all tests will be two-tailed.

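### The analysis section names a within-group paired t test for the MRI and blood outcomes, which the Assessments sections define as KGT-versus-placebo comparisons, and ties no primary between-group test to them

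*Protocol article*

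**What the plan says.** The article describes the contrast of interest in three places, and they do not agree.

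- **Assessments, MRI:** "Changes in CBF and mean levels of NAA/Cr, Glx/Cr, and GABA/Cr, will be compared between KGT and placebo groups, as a primary outcome". This is a between-group contrast, ranked primary.
- **Assessments, Blood testing:** "Changes in mean values of blood biomarker levels will be compared between the KGT and placebo groups". This is also between-group, without the primary label. The Outcome section places the blood biomarkers among the secondary outcomes.
- **Outcome:** the primary outcomes, cognitive and imaging, are worded only as changes from before to after taking KGT or placebo. No contrast between arms is stated for them. Among the secondary outcomes it lists "a comparison of MRI changes between the two groups using age and genotype as covariates". The Abstract gives that comparison the same rank.

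The Data analyses section then gives the tests:

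- **Generic, between groups:** Student's t "test will be used for parametric variable comparisons between the two groups", with Mann-Whitney U for non-parametric variables. No outcome is named.
- **Generic, within group:** the paired t "test will be used for intra-group comparisons", with the Wilcoxon signed-rank test as its non-parametric counterpart.
- **Specific to MRI, blood proteins and cholesterol:** the paired t "test will be used to compare changes in MRI measurements, blood proteins, and cholesterol levels, before and after treatment".
- **Specific to MRI, between groups:** "Linear regression analysis will be used to compare changes in MRI measures, between the study group and the placebo group", with age and APOE genotype as covariates.
- **Threshold:** P < 0.05, two-tailed, for all tests alike.

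**The concern.** The test assigned by name to the MRI and blood outcomes cannot answer the question that the MRI and Blood testing sections ask. By the article's own generic rule, the paired t test is for comparisons inside one arm. It asks whether the mean in that arm moved over 24 weeks, not whether KGT moved it more than placebo did.

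Movement over 24 weeks can have causes common to both arms, such as disease course, the passage of time or drift in measurement. A significant before-after change in the KGT arm therefore cannot be attributed to KGT. A significant change in the KGT arm with a non-significant one in the placebo arm is not a test of the difference either. Because the paired tests carry the same significance threshold and no descriptive label, a report could follow the Outcome and Data analyses wording, present a within-arm P value as the result for a primary outcome, and claim to be per protocol.

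**Working it through.** **Step 1. Match each outcome to the tests the article names for it.**

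| Outcome | Contrast defined under Assessments | Test named for it under Data analyses | Between-group test tied to it by name |
|---|---|---|---|
| MRI (CBF, NAA/Cr, Glx/Cr, GABA/Cr) | KGT vs placebo, primary | Paired t; regression on age and APOE genotype | Only the regression, ranked secondary in the Abstract and Outcome |
| Blood proteins and cholesterol | KGT vs placebo | Paired t | None; only the generic rule can apply |
| SNSB | KGT vs placebo, primary | None by name | None; only the generic rule can apply |

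For SNSB no specific sentence competes with the generic between-group rule. For MRI and blood a specific sentence does, and it names a within-group test.

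**Step 2. Group sizes.** The Sample size calculation section targets 30 and recruits 38 for 20% dropout. This reproduces: 30 / (1 − 0.20) = 37.5, rounded up to 38. With 1:1 allocation that is 30 / 2 = 15 per arm at target and 38 / 2 = 19 per arm as recruited. The article gives no effect size, SD or power, so there is no power figure to reproduce.

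**Step 3. How often a paired test in the KGT arm is significant when KGT does nothing.** Assume the true KGT-placebo difference is zero, change scores are normal, and both arms share a mean change of d standard deviations of the change score. The value of d is an assumption; the article gives none. The paired t statistic then follows a noncentral t distribution with n − 1 degrees of freedom and noncentrality d√n. At two-sided 0.05:

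p = P(|T| > t(0.975, n − 1))

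The critical values are 2.145 for n = 15 and 2.101 for n = 19. With independent arms of equal size, the pattern of KGT significant and placebo not has probability p(1 − p).

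| n per arm | d | d√n | p, KGT arm significant | p(1 − p) |
|---|---|---|---|---|
| 15 | 0.3 | 1.162 | 0.192 | 0.155 |
| 15 | 0.5 | 1.936 | 0.438 | 0.246 |
| 19 | 0.3 | 1.308 | 0.236 | 0.180 |
| 19 | 0.5 | 2.179 | 0.541 | 0.248 |

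**Step 4. The same situation with the between-group test.** A shared shift cancels in the difference between arms, so the two-sample t test on change keeps its nominal 5%. Simulation (100,000 trials per setting, shared shifts of 0, 0.25, 0.5, 0.75 and 1.0 SD, 15 or 19 per arm) gave 4.9% to 5.1% throughout.

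**Step 5. Sensitivity to the assumed shift.** With no shared shift the paired test is significant in 5% of trials, so the problem vanishes numerically. At 0.25 SD it is 15% (n = 15) or 18% (n = 19); at 1.0 SD, 95% or 98%. The pattern of KGT significant and placebo not ranges from about 2% to 25% over shifts of 0 to 1 SD.

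**The case against.** The strongest reply is that the between-group test is already there. The generic Student's t/Mann-Whitney rule stands in the paragraph just before the paired-t sentence and can cover MRI, blood and SNSB variables alike. On that reading the unadjusted t test is the primary MRI comparison, the age/APOE regression is a secondary adjusted analysis, and the paired tests are an addition. This reading is coherent, and it stands as a limit on the point: the article does not restrict these outcomes to within-group testing. A reader might infer that the placebo comparison has been abandoned, or that the primary randomised contrast has been replaced by an uncontrolled one. The article does not support that. Nowhere does it say that a within-arm P value is the test of effect.

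The coherent reading still has to be supplied by the reader. The generic rule names no outcome, the specific sentence does, and the Outcome section's before-after wording for the primary outcomes fits the paired test as readily as the between-group one.

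Three further limits also stand.

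- A reader might add that regression to the mean and practice gain make a shared shift likely, since participants are selected for impairment on the SNSB and retested on it. That argument concerns the SNSB. Nobody is selected on MRI measures or blood proteins, and practice does not affect them, so it cannot be carried over.
- The 19-54% figures rest on an assumed shift. They become a false-claim rate only if the within-arm result is reported as a KGT effect.
- An unadjusted t test on change is valid in a randomised trial. Baseline adjustment is proposed for precision, not to repair bias.

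That this is a condensed article, with any statistical analysis plan not shown, excuses silence. It does not excuse naming a test that cannot deliver the stated contrast.

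**Conclusion.** The point holds as an inconsistency that should be fixed; it is not a must-fix. Data analyses assigns a within-group test by name to outcomes that the MRI and Blood testing sections define as KGT versus placebo. The primary MRI contrast has no between-group analysis tied to it except one ranked secondary, the blood outcomes have none tied to them, and the paired tests are not marked descriptive.

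The size is illustrative. With no drug effect and a shared shift of 0.3 to 0.5 SD of change, the KGT-arm paired test is significant in 19-44% of trials at 15 per arm and 24-54% at 19 per arm, against about 5% for the between-group test. This assumes normal change scores and a shift for which the article gives no figure; with no shift there is no excess. The textual mismatch does not depend on any of these numbers.

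**What to change.** 1. In Data analyses, replace the paired-t sentence. State that for each MRI and blood outcome, and for SNSB in line with the K-MMSE and SNSB section, the test of effect is the between-group difference at week 24 from a linear model adjusted for the baseline value, with its 95% CI.
2. In Outcome, word the primary outcomes as between-group differences in change, to agree with the MRI section, and state the same contrast for the blood biomarkers, to agree with the Blood testing section.
3. State whether the MRI model with age and APOE genotype is the primary analysis or a supporting one, and make the Abstract and Outcome agree.
4. Report within-arm changes as descriptive only (means with SDs), not as tests of effect.

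If the sponsor keeps an unadjusted t test on change, the minimum is one sentence saying that the between-group comparison is the test of effect and that paired tests are descriptive.

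The cost is wording only. Baseline and 24-week MRI, blood and SNSB measurements are already scheduled, so no new data, visits or participants are needed. The change should be dated before unblinding.

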### Adverse events

An undesirable, unexpected sign, symptom, or disease that occurs during the trial will be identified as an adverse event (AE), regardless of any causal relationship with the study intervention. Adverse events will be checked for at every visit, from assessment of participants’ subjective reports and by objective examination, including blood tests and ECGs. Monitoring will also be performed by phone each week during the intervention period, and 4 weeks after the end of treatment. All AEs will be recorded in the CRF by the site investigator and assessed for severity and causality. Details of each AE will be recorded, including start and end date, feature, duration, severity, and causal relationship to the study medication.

Serious adverse events (SAEs) are defined as illness requiring hospitalization, events that result in persistent or significant disability or incapacity, events deemed life-threatening, death, a congenital anomaly or birth defect, or other important medical conditions. If SAEs occur, study participation will be discontinued, appropriate measures will be taken immediately, and the Institutional Review Board (IRB) will be notified as soon as possible. All occurrences of AEs will be monitored until they subside or stabilize.

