#### Safety assessment

Laboratory tests and ECGs will be performed for safety outcomes. Blood levels of AST/ALT, glucose, BUN, Cr, Na, K, Cl, cholesterol, LDH, and CPK will be measured at baseline, 12, and 24 weeks after medication. An ECG will be performed at baseline, and 24 weeks after medication. Vital signs will be recorded at every visit. Any abnormal results in laboratory tests, ECG or vital signs, will be closely monitored. The investigators will call participants by phone 4 weeks after completion of medication, to monitor occurrence of any adverse events.

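### The AE definition requires an event to be unexpected, so foreseen non-serious events can go unrecorded and AE incidence can be under-counted

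*Protocol article*

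**What the plan says.** In the protocol article, the Adverse events section gives the definition: "An undesirable, unexpected sign, symptom, or disease that occurs during the trial will be identified as an adverse event (AE". The sentence goes on to say that this applies "regardless of any causal relationship with the study intervention". AEs are looked for at every visit, "from assessment of participants’ subjective reports and by objective examination, including blood tests and ECGs", and also by weekly phone contact during treatment and once more 4 weeks after it ends. On recording, the section says: "All AEs will be recorded in the CRF by the site investigator and assessed for severity and causality".

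The same section defines serious events by their consequences: "Serious adverse events (SAEs) are defined as illness requiring hospitalization, events that result in persistent or significant disability or incapacity", followed by life-threatening events, death, birth defects and other important medical conditions. Expectedness plays no part in that list.

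The Safety assessment section covers the scheduled measurements: "Laboratory tests and ECGs will be performed for safety outcomes". The chemistry panel "will be measured at baseline, 12, and 24 weeks after medication", and the ECG is done at baseline and 24 weeks. It adds: "Any abnormal results in laboratory tests, ECG or vital signs, will be closely monitored".

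**The concern.** Two adjectives qualify the same noun phrase, so an event must be both undesirable and unexpected to count. The sentence takes care to remove one condition, causality, but leaves expectedness in place, and nothing elsewhere in the article removes it. CRF entry and the grading of severity and causality are tied to being an AE. An investigator who applies the text as written can therefore leave out a complaint because it was foreseen. No list of expected effects is given, so that judgement may differ between staff and over time.

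Safety is a stated aim of the pilot (Background) and a secondary outcome (Outcome), and the findings are meant to support a larger trial (Discussion). AE incidence by arm is an obvious thing for the planners of that trial to take from this one. With so few participants, a handful of omitted events would change it noticeably.

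**Working it through.** The point concerns a definition, so most of the check is a comparison of the sections.

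**Step 1. Conditions attached to each definition (Adverse events section).**

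| Condition | AE | SAE |
|---|---|---|
| Undesirable | required | implied by the listed consequences |
| Causally related | expressly not required | not mentioned |
| Unexpected | required | not mentioned |

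A hospitalization that was foreseen meets the SAE definition and fails the AE definition. SAEs should be a subset of AEs. As worded, they are not.

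**Step 2. How each kind of foreseen event reaches the data.**

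- *Laboratory or ECG abnormality.* It is measured in everyone on a fixed schedule, so the value is collected whatever it is called. Only its grading for severity and causality depends on AE status.
- *Serious event.* It is captured by the SAE definition, expected or not.
- *Non-serious symptom*, such as nausea, diarrhea, abdominal pain or edema. Neither the Outcome section nor the Safety assessment section schedules a measure of these. In this text they reach the record as events only if they qualify as AEs.

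The gap is therefore confined mainly to the third group.

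**Step 3. Numbers in the document.** The only sample-size figure reproduces: 30 / (1 − 0.20) = 37.5, rounded up to 38. At 1:1 this is 38 / 2 = 19 per arm. The point does not depend on it. No AE rate is stated, so the under-count cannot be calculated.

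**Step 4. Can the direction be derived?** Illustration on assumed figures only: 19 per arm, with true AE risks of 40% on KGT and 20% on placebo (risk difference 20 points, risk ratio 2.0). Let *s* be the share omitted as expected.

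- *Same share lost in both arms.* Expected KGT count = 19 × 0.40 × (1 − s). For s = 0, 25%, 50% and 75% this gives 7.6, 5.7, 3.8 and 1.9. The risk difference, 20 × (1 − s), falls from 20 to 15, 10 and 5 points. The risk ratio stays at 2.0.
- *Only the KGT excess is lost.* Risk ratio = [0.20 + 0.20 × (1 − s)] / 0.20, which for s = 25%, 50% and 75% gives 1.75, 1.5 and 1.25.
- *Same absolute amount lost in both arms*, say 10 points of background complaints. The risks become 40 − 10 = 30% and 20 − 10 = 10%. The risk difference stays at 20 points and the risk ratio rises to 3.0.

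Other assumed risks show the same pattern. With s = 50% of the KGT excess lost, the risk ratio falls from 1.5 to 1.25 (30% against 20%) or from 1.67 to 1.33 (50% against 30%).

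In all these cases the KGT AE rate is too low. The effect on the comparison between arms depends on which events are omitted, and the document does not settle that.

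**The case against.** The best defence is that *unexpected* is loose wording for untoward or unintended. It stands beside a clause that sets causality aside, and the next sentence looks for AEs through blood tests and ECGs, which would make little sense if whatever those tests are designed to find were ruled out. No list of expected effects exists by which staff could exclude anything, and the full protocol, which is not shown, may handle expectedness properly. Visits, weekly calls and a follow-up call give ample opportunity to hear of events.

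Much of this stands as a reason to think that the practical effect may be small. It does not repair the text. The article states the definition itself, so this is not detail left to another document. The lack of a list leaves the judgement open without removing it. Frequent contact does not help if an event reported at that contact fails the definition.

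A reader might go further and infer that the safety outcome is biased low, or that the effects the safety panel looks for are not counted. The document does not support either. The safety outcome is blood chemistry and ECG, measured in all participants on schedule, and the AE wording does not touch those values. A reader might also take the exclusion criteria (edema, gastrointestinal symptoms, drugs that can lower potassium or damage muscle) as a list of anticipated KGT effects. The article never calls them that, so the link is plausible but inferred.

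**Conclusion.** The point holds as a defect of definition with a limited reach. Taken literally, the wording keeps foreseen non-serious undesirable events out of the AE record and out of grading, and it is inconsistent with the SAE definition beside it. What is at risk is AE incidence, chiefly for symptoms with no scheduled safety measure. The laboratory and ECG outcomes and the capture of serious events are not at risk.

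The size of any under-count cannot be derived, and no omission has been shown to have occurred. It depends on how investigators apply one word. A tempting further step is to say that the comparison between arms is pulled towards no difference because anticipated effects fall mainly on KGT. That needs an assumption which the document does not supply: participants, assessor and researchers are blinded, and the illustration above shows that the risk ratio may fall, stay the same or rise. The correction is worth making because it costs almost nothing and protects AE ascertainment in a pilot that has safety as a stated aim.

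**What to change.** Delete *unexpected* from the AE definition. Keep the present time window (events during the trial) and the clause that sets causality aside. Record expectedness as a separate attribute of each event, alongside severity and causality. The AE and SAE definitions then nest.

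The article reports 33 participants already enrolled. Check their existing visit and phone-contact records for undesirable events that were left out under the present wording, and add any that are found.

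The cost is a one-word amendment, one extra CRF field and a small record check. The reported AE rate may rise slightly.
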